### Aims and objectives

The Tromsø Study is a large ongoing population-based cohort study with five previous health studies undertaken between 1974 and 2001 (Table 2). This protocol outlines a planned study in the sixth Tromsø Study (Tromsø VI), which will be carried out in 2008–2009.

**Table 2 T2:** Participation in five previous Tromsø Studies, 1974 to 2001

			**No. invited**		**No. attending**		**Attendance (%)**	
			
**Study**	**Year**	**Year of birth**	**Men**	**Women**	**Men**	**Women**	**Men**	**Women**
Tromsø I	1974	1927–1956	8 867		6 595		83	
Tromsø II	1979–1980	1925–1959^1^	11 481	9 959	8 477	8 144	73.8	81.8
Tromsø III	1986–1987	1925–1966^1^	14 539	12 877	10 413	10 189	71.6	79.1
Tromsø IV	1994–1995	<1970	18 480	19 078	12 865	14 293	69.6	74.9
Tromsø V	2001	<1972^2^	4 636	5 717	3 511	4 619	75.7	80.8

^1^From 1930 onward for women. ^2^Full birth cohorts were not included. See text for description.

The Tromsø Study is well suited for sleep studies in the general population, with its unique availability of multiple objective biological measures, as well as current medication use, physical and psychosocial functioning – which will allow research on independent correlates of sleep disturbances.

This protocol describes two main aims:

1) To present descriptive sleep data of a community-based sample representative of the general population of northern Norway.

2) To examine sleep outcome variables against potential explanatory variables examine, both within a cross-sectional approach, as well as retrospectively in a longitudinal study exploring development of sleep characteristic in subjects having attended two or more of the Tromsø studies between 1974 and 2009.

We plan to merge data on an individual level from the Tromsø VI Study with data from the Norwegian Prescription Database (NorPD), which is a national registry including data for all prescription drugs issued at Norwegian pharmacies since 2004 [55]. This will enable research on drug-related sleep complaints.

In addition to the two main aims outlined in this protocol, we are planning a follow-up controlled cohort-study, which will include subjects with sleep complaints recruited in Tromsø VI. This prospective study will aim to investigate possible causal factors of insomnia, and will be described in detail in a later protocol.

## Methods

### Setting

The current study will be performed in a non-institutionalized general population in northern Norway, aged 20 to 90 years. Samples will be drawn in a two-stage procedure, described below.

In the first stage, data from all eligible participants in the Tromsø VI Study will be assessed, in order to describe sleep disturbances and their associated risk factors. In the initial survey, self-reported sleep disturbances will be addressed in questionnaire 1 (Q1), with one single question; "During the last 12 months, how often have you experienced sleep disturbances?", answered with a four-item response: *"never", "1–3 times per month", "once a week" *or *"more than once a week"*. In this initial screening, the selection criterion for sleep disturbances will be *"more than once a week"*.

In the second stage, all participants who report sleep disturbances ("*more than once a week"*) will be invited to a second cross-sectional survey, where sleep complaints and daytime sleepiness will be mapped, using a sleep assessment questionnaire (questionnaire 2 = Q2) described below. A pair-matched control group (matched for age and gender) will be recruited among the remaining participants (those without sleep complaints).

Assuming that the prevalence of sleep complaints in the Tromsø VI Study corresponds to previous estimates for the general population, we expect to include 10 to 15% of the total study population into the sleep complaint group.

In order to analyze possible seasonal effects due to the natural annual light-dark cycle in the artic, we will examine a random half of the participants in the sleep complaint group and control group with Q2 in the part of the year with the highest levels of environmental light (May-June), and examine the remaining participants with Q2 in the part of the year with the lowest levels of environmental light (November-December).

### Questionnaires

All participants in Tromsø VI will be asked to complete an extensive questionnaire (Q1), including demographic data, socioeconomic variables, subjective health perception, quality of life, current medical diagnoses and symptoms, use of prescription drugs and OTC-drugs, use of and satisfaction with health services. In addition, biological markers (i.e. blood samples, height, weight, blood pressure) will be collected.

The sleep assessment questionnaire (Q2) will among other items include the Epworth Sleepiness Scale (ESS) and the Pittsburgh Sleep Quality Index (PSQI).

The ESS [8] is useful in measuring the frequency of daytime sleepiness, and has been used in numerous studies [56-60]. ESS evaluations have demonstrated significant association between daytime sleepiness and insomnia [59], and have allowed quantitative analysis of the effects of pharmacologic and non-pharmacologic therapies on daytime sleepiness in poor sleepers [56,60]. Subjects are instructed to rate the chance of dozing off or falling asleep in eight different "real-life" circumstances. Grading of each item ranges from 0 to 3 and the maximum total score reaches 24. Values over 10 are regarded as indicative of excessive daytime sleepiness [8,61]

The PSQI is a self-rated questionnaire assessing sleep quality and disturbances lasting for more than 1 month [62]. This subjective measure has been validated against polysomnography (PSG) [62-64], which is considered the gold-standard for measuring sleep disturbances [65]. The PSQI is now one of the most commonly used assessments for the evaluation of insomnia severity in sleep research [65,66], and its validity has been demonstrated for patients with mental disorders [62,67], for patients with different somatic diseases [68], and for healthy elderly subjects [63].

Sleep assessment tools, such as ESS and PSQI, are usually treated as binary variables in large population-based studies, according to their cut-off values for "normal" vs. "insomnia". For clinicians, however, a more accurate grading of insomnia is usually needed and the scales are used as continuous variables in order to grade insomnia into e.g. "mild", "moderate" or "severe".

In addition to the PSQI and ESS, Q2 will also address presence of restless legs, nightmares, shift-work and self-reported strategies for coping with insomnia.

### Population

The Norwegian city of Tromsø is situated 70° north of the equator and north of the Arctic Circle. It is the largest city in northern Norway, with approximately 60.000 inhabitants. The aims of the repeated Tromsø studies (Table 2) are to investigate determinants for chronic diseases and to identify potentially modifiable determinants that may contribute to the development of preventive strategies.

In 2001, the size of the study population was 8.130 persons, which was considerably less than most previous Tromsø studies. This was a result of a steered invitation policy to those individuals attending two sub-populations in the 1994/1995 Study.

The size of the population to be invited in the forthcoming Tromsø VI Study is still not established, but is expected to be about 12.000 in the age from 20 to 90 years.

### Outcome measures

Outcome measures in the first part of this study will be the prevalence of sleep disturbances as reported in the initial questionnaire (Q1) containing a four-item response option, where sleep disturbance is defined as the average occurrence of sleep problems *"more than once a week"*.

In the second part of the study, sleep characteristics will be further mapped by a sleep questionnaire (Q2), sent by mail to subjects in the sleep complaint group and in an approximately equal-sized control group. Recruitment, pair matching, questionnaire logistics (including reminders) will be handled by the Tromsø Study's central body, situated at the University of Tromsø. Outcome measures are summarized in Table 3.

**Table 3 T3:** Sleep outcome variables, potential explanatory variables and their pre-specified associations in the Tromsø Study

*Sleep outcome variables against potential explanatory variables*	*Pre-specified associations*	*References*
Initial screening of all eligible participants in the Tromsø Study:		
• Prevalence of sleep disturbances reported in the initial questionnaire (Questionnaire 1) containing a four-item response option, where sleep disturbance is defined as the average occurrence of sleep problems *"more than once a week"*.	10 to 50% in the adult population.	[2, 76]
• Sleep disturbances and their possible relationships, including demographic variables, health-related variables, and lifestyle and socioeconomic variables, and biological markers.	Increased risk for impairments in health, decreased quality of life and increased healthcare utilization.	[19, 65, 77-80]

Further mapping with validated sleep assessment questionnaires among subjects with sleep complaints selected in the initial screening and their control group:		
• Sleep outcome variables related to the use (dose and frequency) of specific prescription drugs, derived from the Norwegian Prescription Database (NorPD).	Frequent use of hypnotics and over-the-counter (OTC) medications.	[36, 37]
• Sleep outcome variables related to socioeconomic variables.	Insomnia related to unemployment and socioeconomic deprivation, more common in women, elderly and individuals living alone.	[81, 82]
• Sleep outcome variables and excessive daytime sleepiness related to objective medical diagnosis, such as diabetes and coronary disease.	A possible link between short sleep, diabetes mellitus, coronary heart disease and all over mortality.	[21, 25-28]
• Sleep outcome variables related to the diagnosis of restless legs.	Relation between symptoms of restless legs and insomnia	[15]
• Sleep outcome variables related to self-reported complaints of musculoskeletal symptoms.	Relation between symptoms of musculoskeletal symptoms and insomnia	[83]
• Sleep outcome variables related to self-reported psychiatric symptoms	Elevated risk of depression and anxiety disorders in people with persistent insomnia	[58, 77, 84-86]
• Sleep outcome variables related to self-reported frequency of nightmares.	Possible association between nightmares and being a woman, feeling depressed after a poor night's sleep, and complaining of a long sleep latency.	[87]
• Sleep outcome variables related to excessive daytime sleepiness and reported actual sleep length.	Daytime sleepiness inversely related to hours of sleep and positively related to the ease of falling asleep at night, especially among young adults.	[88, 89]
• Sleep outcome variables and excessive daytime sleepiness related to subjective perceptions of pain	Chronic pain populations are more likely to experience chronic insomnia, sleep maintenance problems, and/or nonrestorative sleep.	[17, 35, 90]
• Sleep outcome variables and excessive daytime sleepiness related to doctor-seeking behaviour.	Although insomnia is related to more consultations with GPs, many individuals hesitate to consult their doctor about insomnia	[72, 82]

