### Statistics

Below, we describe the most probable statistical approaches in the evaluation of associations between self-reported sleep disturbances and exposures. However, in the course of analyses, and with further knowledge of the actual data set, the statistical approach may be supplemented and/or modified. SPSS version 14.0 will be used for statistical analyses. STATA 10 is used for sample size and power calculations.

Age adjustments in groups of subjects with sleep complaints will be performed by the direct method with the Norwegian population serving as standard population.

We plan to carry out series of tabular analyses, tabulating our outcome variables against potential explanatory and confounding variables. These tabulations will guide further analyses. A matched regression analysis will be done using conditional logistic regression in SPSS. For each model we will compare the results of the univariate analyses to those of multivariate analyses. We aim to construct credible parsimonious explanatory models, which will be critiqued using residual analysis, and the Hosmer-Lemeshow goodness of fit test.

Relevant variables that reach significance in bivariate analyzes, will be entered into a multiple logistic regression analyses to determine their influence on sleep outcome variables.

Some of the variables might have missing values. One possible way to deal with missing values is by multiple imputation. To include most of the observations in the model, the missing values may be included after an imputation procedure in SPSS, where the missing value is replaced by the mean of the non-missing values for that variable.

From the first initial screening to the subsequent mapping with the extensive sleep-questionnaire, it may happen that some subjects defined as "cases" reach normal values and vise versa. These subjects and their matched control/case will be excluded from later analyses.

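### Stage-one risk-factor models appear to use only the top level of the four-level Q1 sleep item; an ordinal analysis alongside the binary one would recover information, mainly for uncommon exposures (minor)

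*Protocol article*

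**What the plan says.** - **The item.** Under Setting, Q1 has one sleep question, "answered with a four-item response": never, 1–3 times per month, once a week, or more than once a week.
- **The purpose of stage one.** Also under Setting: "data from all eligible participants in the Tromsø VI Study will be assessed, in order to describe sleep disturbances and their associated risk factors".
- **The definition.** Outcome measures and the first row of Table 3 describe the item as "containing a four-item response option, where sleep disturbance is defined as the average occurrence of sleep problems" at the highest of the four levels. This is given as the prevalence outcome, and Setting uses the same cut to select people for stage two.
- **The association analysis.** The second row of Table 3, still under the initial screening of all participants, reads "Sleep disturbances and their possible relationships, including demographic variables, health-related variables, and lifestyle and socioeconomic variables, and biological markers". It does not repeat the cut.
- **Expected share above the cut.** Setting: "we expect to include 10 to 15% of the total study population into the sleep complaint group". Table 3 gives a wider expectation, "10 to 50% in the adult population".
- **The model.** Statistics says that variables significant in bivariate analysis "will be entered into a multiple logistic regression analyses to determine their influence on sleep outcome variables". It also names conditional logistic regression for the matched data and the Hosmer-Lemeshow test. It names no model for an ordered outcome. The section presents its methods as the most probable ones and allows them to be supplemented or changed.

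**The concern.** The cut is needed to state a prevalence and to choose the stage-two group. It is not needed to relate sleep frequency to risk factors in the whole cohort. If 10 to 15% fall in the top category, the other 85 to 90% are treated as alike, although the question has already sorted them into three ordered groups.

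A split this far from the middle is statistically weak when an association runs through the whole scale. Odds ratios then have wider intervals than the collected data allow. Because entry to the multiple model depends on bivariate significance, an uncommon exposure missed at that step is not examined further. A binary outcome also cannot show whether an association is graded across frequency levels.

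**Working it through.** **The plan's own figures.** The only sample sizes given are for the stage-two pairs, and they reproduce with n = (SD × 3.2415 / difference)², rounded up, where 3.2415 = 1.96 + 1.2816:
- PSQI: (4.58 × 3.2415 / 2)² = 55.1, so 56.
- ESS: (5.9 × 3.2415 / 2)² = 91.4, so 92.
- BMI: (5.7 × 3.2415 / 1)² = 341.4, so 342.

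They do not bear on stage one, for which no power figure is given.

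**Inputs.** N = 12,000 (Recruitment and randomization); top category 10 to 15% (Setting); two-sided 0.05 (Statistics). Assumed, because the article does not give them: the split of the three lower categories, the exposure prevalence e, and the odds ratio (OR).

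**Formulas.** Information on a log odds ratio near the null:
- binary cut: N·e(1−e)·p(1−p), where p is the top-category share;
- four levels under proportional odds: N·e(1−e)·(1 − Σpₖ³)/3.

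Power = Φ(|log OR|·√information − 1.96).

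**Worked case, split 60/20/10/10%.** Binary: 0.10 × 0.90 = 0.090. Ordinal: (1 − 0.216 − 0.008 − 0.001 − 0.001)/3 = 0.258. Ratio 2.87. For e = 5%, N·e(1−e) = 570. At OR 1.25 (log 0.2231):
- binary: Φ(0.2231 × √51.3 − 1.96) = 36%;
- ordinal: Φ(0.2231 × √147.1 − 1.96) = 77%.

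**Four assumed splits, 5% exposure, OR 1.25:**

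| Split, never to top (%) | Information ratio | Binary power | Ordinal power |
|---|---|---|---|
| 45/30/12.5/12.5 | 2.68 | 42% | 82% |
| 60/20/10/10 | 2.87 | 36% | 77% |
| 35/35/15/15 | 2.37 | 48% | 83% |
| 75/10/5/10 | 2.13 | 36% | 65% |

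The OR detectable with 80% power falls from 1.39–1.48 (binary) to 1.24–1.31 (ordinal).

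**Sensitivity to the lower split.** With 10 to 15% at the top and the rest divided equally, 50/35/15, 60/30/10 or 80/15/5, the binary cut keeps 0.29 to 0.56 of the ordinal information. With 95/4/1 it keeps 0.72 to 0.81, an ordinal-to-binary ratio of about 1.2 to 1.4.

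**Sensitivity to prevalence.** Over the same five divisions, the cut keeps 0.67 to 0.93 with 30% in the top category and 0.87 to 0.98 with 50%.

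**Common exposures.** At OR 1.25 and a 20% exposure, the binary model already has 83 to 94% power over the four tabled splits. At a 50% exposure it has 96 to 99%.

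**Departure from proportional odds.** Simulation with 12,000 participants, 5% exposure and 4,000 runs, comparing a two-proportion score test with a tie-corrected Wilcoxon test (the proportional-odds score test). ORs are listed from the lowest to the highest cut. The first three rows cover the first, second and fourth tabled splits; the last two rows give ranges over all four.

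| ORs at the three cuts | Binary vs ordinal power |
|---|---|
| 1.30/1.30/1.30 | 0.60 vs 0.92; 0.53 vs 0.90; 0.54 vs 0.81 |
| 1.20/1.25/1.30 | 0.60 vs 0.75; 0.54 vs 0.69; 0.54 vs 0.56 |
| 1.15/1.20/1.30 | 0.61 vs 0.58; 0.55 vs 0.51; 0.54 vs 0.39 |
| 1.05/1.15/1.30 | 0.53–0.65 vs 0.13–0.29 |
| effect at the top cut only | 0.52–0.66 vs 0.06–0.09 |

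The ordinal test gains when the association is spread over the scale and loses, sometimes heavily, when it is concentrated at the top.

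**The case against.** - **The cut is written for prevalence and selection.** Table 3's second row does not restate it. This stands as a caution: that the cut governs the association models is an inference. It is a reasonable one, because the article has no other definition of the term and names only logistic models.
- **The statistics section is open to change.** This also stands. An ordinal analysis is permitted; it is simply not planned. The clause lowers the severity. It does not remove the benefit of naming the analysis before the data are seen.
- **A binary odds ratio answers a legitimate question.** It describes being a case as the study defines one, and the same group goes on to stage two. This stands, and it is why the binary result must remain.
- **The gain depends on assumptions that the article does not supply.** This stands, as the sensitivity results show.

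A reader might infer that the ordinal model should replace the binary one as the lead analysis. The documents do not support that: they give no expected effect pattern, and the ordinal test has less power under patterns that are quite plausible. A reader might also infer that a frequency gradient belongs to the stated aims. The aims speak of descriptive sleep data and of sleep outcomes against explanatory variables, and mention no gradient. Nor should specific drug groups and diagnoses such as diabetes or coronary disease be taken as the main casualties in stage one. Q1 does collect diagnoses and drug use, but Table 3 places those analyses in the stage-two mapping.

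**Conclusion.** The point holds as a minor one. As the article reads, the stage-one association models would use only the top level of an ordered item and treat weekly problems as none. With 10 to 15% in that level and roughly proportional odds, about half or more of the information can be lost; under an extreme lower split the loss is about a fifth to a quarter (1 − 0.81 to 1 − 0.72). The practical cost falls on uncommon exposures of about 5%; common ones are well powered with 12,000 participants. The conclusion rests on an assumed lower split, on the Setting section's 10 to 15% rather than the upper part of Table 3's range, and on associations that extend below the top cut. Where they do not, the binary analysis is the better one. This is a missed opportunity in the analysis plan and not an error or contradiction.

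**What to change.** Keep the highest response level as the definition for prevalence, for stage-two selection and for the case odds ratio. Add a sentence to Statistics that pre-specifies, beside the binary stage-one models, a proportional-odds or partial proportional-odds model of the four-level Q1 response with the same covariates. State that proportionality will be checked and that cut-specific odds ratios will be reported where it fails.

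The cost is one sentence and modest extra analysis. The four levels are already collected, and no participants are added. There are two downsides: an assumption to check, and a second odds ratio that describes a shift in frequency rather than being a case, so the report must keep the two apart.

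### The sleep-outcome models make no distinction between antecedents and consequences of poor sleep, so entering doctor-seeking, healthcare use or quality of life would bias the odds ratios of risk factors that also affect them

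*Protocol article*

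**What the plan says.** Table 3 (protocol article, Outcome measures) is titled "Sleep outcome variables, potential explanatory variables and their pre-specified associations in the Tromsø Study". Sleep is therefore the outcome, and the other variables are potentially explanatory. Three rows matter here:

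- **Initial screening, second row.** Sleep disturbance is set against demographic, health-related, lifestyle, socioeconomic and biological variables. The predicted association is "Increased risk for impairments in health, decreased quality of life and increased healthcare utilization".
- **Doctor-seeking row.** The analysis is "Sleep outcome variables and excessive daytime sleepiness related to doctor-seeking behaviour". The prediction is "Although insomnia is related to more consultations with GPs, many individuals hesitate to consult their doctor about insomnia".
- **Psychiatric row.** The analysis is "Sleep outcome variables related to self-reported psychiatric symptoms". The prediction is "Elevated risk of depression and anxiety disorders in people with persistent insomnia".

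Under Questionnaires, the first questionnaire collects "subjective health perception, quality of life, current medical diagnoses and symptoms" and use of health services from all participants.

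The Statistics section plans tabulations, a matched conditional logistic regression, a comparison of univariate with multivariate results for each model, and explanatory models. Relevant variables that are significant bivariately "will be entered into a multiple logistic regression analyses to determine their influence on sleep outcome variables". It gives no criterion for relevance and no ordering of variables in time or cause. It allows the approach to be modified once the data are known.

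**The concern.** Some predictions in Table 3 run from poor sleep to the other variable, while the regression reads the other variable as an influence on sleep. A bivariate test cannot tell a cause from a consequence. With about 12,000 participants expected, a clear consequence is very likely to pass it.

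A variable that both poor sleep and a risk factor affect is a collider. Holding it fixed induces an artificial association between the two. Chronic disease and pain are the obvious examples: each may disturb sleep, and each also sends people to the doctor and lowers quality of life. With doctor-seeking or quality of life in the model, the adjusted OR for disease or pain no longer measures its relation to sleep.

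At stake is the second aim, relating sleep outcomes to explanatory variables, and the ambition under Aims and objectives to identify independent correlates. A true risk factor could be reported as weak or absent.

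**Working it through.** The documents give no effect sizes on this point, so there is no figure of the plan to reproduce. The planned pair counts play no part. All effects below are assumptions.

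**Set-up.** X is a binary risk factor, S is sleep disturbance and C is a binary consequence. S multiplies the odds of C by a, and X multiplies them by b. The odds of C are o when S and X are both absent.

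**Formula.** In a logistic model of S on X and C,

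adjusted OR of X = true OR × F, with F = (1 + ao)(1 + bo) / [(1 + o)(1 + abo)].

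The numerator minus the denominator equals −o(a − 1)(b − 1). Three things follow:

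- If b = 1 (X does not affect C), F = 1 and there is no bias.
- If a and b both exceed 1, F is below 1, so an OR above 1 is pulled down.
- F contains neither the prevalence of S nor that of X, so sampling on sleep status does not alter it.

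For several consequences that are independent given S and X, the factors multiply.

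**Healthcare use alone**, a = b = 2, baseline 25% (o = 1/3):
F = 1.6667² / (1.3333 × 2.3333) = 2.7778 / 3.1111 = 0.893. A true OR of 1.5 becomes 1.34.

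**Weak set**: quality of life a = b = 2 at baseline 20% (o = 0.25), healthcare use a = b = 1.5 at baseline 25%:
F = [1.5² / (1.25 × 2)] × [1.5² / (1.3333 × 1.75)] = 0.900 × 0.964 = 0.868. A true OR of 1.5 becomes 1.30, and 1.3 becomes 1.13.

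**Strong set**: quality of life a = b = 3 at 20%, healthcare use a = b = 2 at 25%:
F = [1.75² / (1.25 × 3.25)] × 0.893 = 0.754 × 0.893 = 0.673. A true OR of 1.5 becomes 1.01, 1.3 becomes 0.87 and 2.0 becomes 1.35.

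For a true OR of 1.5, simulations with these odds ratios gave 1.32 to 1.35 (healthcare use alone), 1.30 to 1.31 (weak) and 1.00 to 1.03 (strong). In simulated samples of 12,000, power to detect the true OR of 1.5 fell from about 100% to 3–4% under the strong set. Under the weak set it stayed near 98%, so the harm there is a biased estimate and not a missed association.

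**Stronger single consequence**, baseline log-odds −1.2 (o = 0.301):

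| a (sleep) | b (risk factor) | F | True 1.5 becomes | Simulated, n = 400,000 |
|---|---|---|---|---|
| 3 | 2 | 0.835 | 1.25 | 1.26 |
| 5 | 3 | 0.664 | 1.00 | 1.00 |
| 5 | 5 | 0.566 | 0.85 | 0.86 |
| 5 | 1 | 1.000 | 1.50 | 1.47 (1.46 unadjusted) |

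**Three continuous consequences**, each shifted d_S standard deviations by S and d_X by X: F = exp(−3 × d_S × d_X). With d_S = 0.5 and d_X = 0.2, F = exp(−0.30) = 0.741 and 1.5 becomes 1.11. With d_X = 0.5, F = exp(−0.75) = 0.472 and 1.5 becomes 0.71. Simulation gave the same values.

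**The case against.** **The plan is flexible and associational.** It describes probable approaches, enters only relevant variables, and defers causal factors to a later prospective study. This is fair as far as it goes. But relevance is not defined, and the present text already speaks of influence and explanation, which is how mutually adjusted ORs will be read.

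**Univariate results will stand beside adjusted ones.** In the set-up above the univariate OR is the true one, so the shift would be visible. It would look exactly like the removal of confounding, however, and the adjusted figure would probably be preferred.

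**Quality of life is not listed as explanatory.** This stands. It appears among the predicted associations and in the first questionnaire. Its entry into a joint model is possible but not stated. Doctor-seeking is the variable that Table 3 names outright.

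**The direction for psychiatric symptoms is open.** This stands too. The Background says it is hard to tell which comes first, and Table 1 lists anxiety and depression among factors related to chronic insomnia. Barring them from every sleep model could itself leave confounding. If depression precedes both pain and poor sleep (assumed ORs of 3), a null pain effect shows as 1.24 to 1.26 without depression in the model and 1.00 to 1.02 with it.

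**The predicted associations are still estimated.** A reader might infer that the link from sleep to its consequences is lost because sleep is the dependent variable. For binary variables the OR is symmetric. With true sleep-to-consequence ORs of 3 and 2, the sleep model returned 2.95 and 2.00. The number survives, and only its reading as an influence on sleep is wrong.

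**Conclusion.** The concern holds in a limited form. Followed as written, the entry rule admits consequences of poor sleep to models meant to explain poor sleep, and doctor-seeking is a named candidate. The odds ratios of risk factors that also affect those consequences would then be biased.

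Under the assumed effects, a true OR of 1.5 falls to about 1.3 with the weak set or healthcare use alone, and to about 1.0 with the strong set. These figures rest on assumed effects, assumed baseline rates and consequences that are independent given sleep and the risk factor.

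A reader might infer that every coefficient is biased, or that true risk factors will generally be erased or reversed. The documents support neither. A factor with no effect on the consequence is untouched, and reversal appeared only for smaller true ORs or stronger effects. Nor is this a fault that any selection rule would share, because a rule based on causal order would remove it. It should be settled before the models are fitted.

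**What to change.** 1. Add a column to Table 3 marking each variable as antecedent, consequence or bidirectional.
2. Keep clear consequences (doctor-seeking, healthcare use, quality of life) out of the sleep-outcome models used to judge risk factors. Report them in separate models with sleep disturbance as the exposure.
3. In the Statistics section, choose the remaining adjustment variables by this ordering and not by bivariate p-values alone.
4. For bidirectional variables (depression, anxiety, other psychiatric symptoms, general health), report the sleep models with and without them. Where earlier Tromsø surveys hold the data, use them to establish which came first; the longitudinal part of the second aim already draws on those surveys.

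The cost is a short rewrite, a few more regressions and two estimates to present and explain for each bidirectional variable. No new data are needed.
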